### Product Acquisition/Software Development

A robotic text messaging software will be developed in conjunction with a contracted third party, Dimagi, Inc. (Charlestown, MA). The software will be built on Dimagi’s existing RapidSMS platform, an open source framework for SMS and web integrated applications [25].

We will work with Dimagi to build into RapidSMS functionality that will allow the software to send out pre-programmed text messages to the intervention group at the time of day and in the language that participants will have determined as most convenient for receiving text messages. Dimagi, Inc. will be responsible for installing the software on site in Kenya and for testing.

Schematic depicting incoming and outgoing flow of SMS

|  |
| --- |
|  |

### Text Message Formulation/Scripting

Text messages will follow a pre-defined script (appendix V) and will be limited to a template of not more than 160 characters (the maximum number of characters allowed for a single text message). The contents of each message as provided in appendix V are draft messages. We may amend the actual wording (before study initiation) based on responses after field testing as well as expert advice from our behavioral scientists.

Text messages will be sent in the participant’s preferred language from a choice of English, Swahili or Dholuo. The text messages will not include the participant’s name, clinic number or HIV status in order to maximize confidentiality.

### Text Messaging Regimen

The text messaging software will be programmed to send out one text message daily to participants in the intervention arm for the first seven days post-procedure. After the first seven days, a text message will be sent on each of days 8, 14, 21, 28, 35, 41 and 42. Each message will be different depending on which post-procedure day it will be for the recipient (per appendix V). Individual text messages will be sent out at the time of day, and in the language, that a participant will have determined as most convenient for receiving text messages.

Participants from either arm who have questions or concerns about their circumcision will call the clinic hotline number that is routinely issued to all men who undergo circumcision. The text messaging software will be set up to handle only text messages and not voice calls.

### Shared Phones

Cases may arise where participants in the intervention arm share their phone with other people. The study will NOT send out personal health information such as HIV status as part of any text message. All study procedures will be thoroughly explained to participants. Participants will be given examples of text messages they may receive and will be asked to give consent only if they find the messages acceptable to be sent to their phone, whether shared or not.

### Cost of Intervention

Because the SMS system is only one way, there is no cost to the study subjects except the cost of sending the registration message. At enrollment, we will load each participant’s phone with airtime worth twenty Kenya shillings (KSh.20) immediately prior to registration. This system will ensure that participants do not bear any costs related to sending or receiving text messages related to this study.

### Storage and Security of Software/Hardware for Delivering Intervention

The computer hardware and software used to house the robotic text messaging software will be kept in a secure room with access limited only to authorized staff. All computers and databases will be password-protected with limited access. Daily backup of the data will be done by a designated study staff.

# STUDY CLINIC VISITS AND PROCEDURES

Participation in this study requires only a single clinic visit at 7 days, followed by a brief questionnaire at 42 days delivered via a phone call.

## Screening Visit

As part of the Kenya Ministry of Health’s MC program, community mobilization is done using a variety of methods, including radio announcements, posters, fliers, mobile vans and drama shows. Men interested in undergoing MC then visit clinics of their choice for education on male circumcision, HIV testing and counseling, booking according to the clinic schedule, and consent and performance of the procedure. Mobilization for this study will be done from among men who will have undergone circumcision at selected sites in Kisumu East and West operated by the Nyanza Reproductive Health Society. All men who meet the study inclusion criteria will be invited to participate.

After the circumcision procedure, patients usually have a 30-minute recovery period. During this time, patients are monitored for effects of surgical trauma and any early complications that may arise. At the end of this recovery period, post-operative care instructions are given verbally and in writing, and the patient discharged.

For this study, study staff will approach men for possible enrollment immediately after discharge but just before a potential participant leaves the recovery room. Study staff will introduce the study to a potential participant by describing the purpose of the study, the anonymity of study data and the participant’s right not to answer any questions. Men who agree to be screened will be led to a separate private counseling room away from the recovery room in order to determine eligibility using the eligibility checklist (appendix 2).

## Enrollment Visit

Enrollment into the study will occur on the same day as screening. While still in the private counseling room, participants who are found to be eligible will be offered enrollment into the study. Study procedures will then be described in detail and participants asked to provide written informed consent prior to enrollment. The informed consent form will also request participants’ permission to access their MC clinic records. The informed consent process is described in section 10.1 below.

After the informed consent process, study staff will abstract demographic information from a participant’s clinic file. Data collected will include *client number, mobile phone number, date of MC, date of birth, ethnic origin, district of residence, sub-location/estate of residence, education level, employment status, marital status, religion, age at first sex, number of sex partners in last month, whether subject has ever been tested for HIV, whether client was given condoms, how client learnt about MC services, referral source, and cadre of person who performed procedure.* HIV status and/or test results will NOT be collected as part of this study. Study staff will also administer a brief questionnaire to all participants (appendix III)*.*

Following enrollment, participants will be randomized to either of the study arms. Randomization procedures are described in detail in section 3.5 above. Participants’ mobile phone numbers will be confirmed using an SMS-based registration system. This will involve sending a text message from a participant’s phone to a phone number controlled by our robotic software. The text message will contain the time of day that they find most suitable for messages to be sent to them as well as the language in which they prefer to receive text messages (from a choice of English, Swahili, or Dholuo). Upon receiving this initial text message, the software will decipher the contents and also store the subject’s phone number. The software will have been pre-programmed to send specific text messages to those in the intervention arm, one on each day at the time and in the language specified by the subject for the first 7 days post-procedure. Details are provided in section 5 below. Participants will be reminded of all study procedures again before leaving the clinic.

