### Allocation concealment

As potential subjects are identified, a research assistant will be notified to assess eligibility. Once a subject is deemed eligible for enrolment, has given the necessary informed consent, has been enrolled, has responded to a brief questionnaire, and has had his demographic information abstracted from his clinic records, the research assistant will issue the next in a series of sequentially numbered, sealed, opaque envelopes containing group assignment [24]. The participant’s clinic number will be written on the envelope, and the participant will be required to open and read the treatment assignment in the presence of the research assistant, who will then enter the group assignment into a database and store the envelope. If a participant is unable to read, the research assistant will read the group assignment on his behalf.

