**Study Registration Module**

SMS-based registration: SMS containing *Study Arm, time to send SMS, preferred language*

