**Enrollment Module (SMS-based registration)**

Assign Study ID number

Complete electronic enrollment form

Participant found eligible; informed consent obtained

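### SMS registration is placed after the envelope is opened; completing it before allocation would avoid randomising men the messaging system cannot reach

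*Protocol*

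**What the plan says.** Three places fix the order of steps.

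- **Allocation concealment (5.1)** lists what precedes the envelope: eligibility, consent, enrolment, a short questionnaire and abstraction of demographic data. SMS registration is not on the list. Once the envelope is issued, "the participant will be required to open and read the treatment assignment in the presence of the research assistant". The arm is recorded electronically at that point.
- **Enrollment Visit (6.2)** states "Following enrollment, participants will be randomized to either of the study arms" and afterwards that participants' "mobile phone numbers will be confirmed using an SMS-based registration system". It gives the content of the text as preferred time of day and language. Delivery depends on this step: "Upon receiving this initial text message, the software will decipher the contents and also store the subject’s phone number".
- **Schematic of the text messaging protocol (5.2), Study Registration Module** describes the content differently: "Study Arm, time to send SMS, preferred language". A text that carries the arm cannot be sent before the arm is known.

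One label could point the other way. The schematic also has a box titled "Enrollment Module (SMS-based registration"), which holds eligibility, consent and the study ID. The order of the boxes cannot be recovered from the available text, so this label does not outweigh the two narrative sections.

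The primary analysis is by intent-to-treat (10.2, Inferential analyses).

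**The concern.** Registration is the first test that a man's phone and number work with the messaging system. The inclusion criteria ask that he own a text-capable phone and have it with him; they do not ask for a tested link. Because the test follows allocation, a failure cannot keep him out of the trial. If it is not put right on the spot, an intervention man may go through follow-up without messages while he counts, properly, in the intervention arm. The observed effect then moves toward the null, and the trial loses power for a reason that a different order of steps would largely remove.

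A second point is weaker. Registration is done when the research assistant and the participant both know the arm, and only intervention men need it in order to be messaged. Persistence with a failed text could therefore differ. The day-42 telephone interview supplies the Objective 2 outcome in both arms, so unequal care over numbers could in principle affect follow-up.

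**Working it through.** **Inputs from the protocol (10.1 and 10.2).** Two-sided 5% test, 1:1 allocation. Objective 1: control risk 0.57, relative risk 0.83, 600 per arm, at least 90% power (table entry 557). Objective 2: control risk 0.225, relative risk 0.70, 532 per arm after about 11% loss, at least 80% power (table entry 532).

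**Input that is assumed.** The share f of the intervention arm that is never messaged. The protocol gives no figure, so a range is shown.

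**Step 1: reproduce the planned sizes.** The protocol's formula is not legible in the available text. The usual pooled-variance formula without continuity correction is

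n = [1.96·√(2p̄(1−p̄)) + zβ·√(p0(1−p0) + p1(1−p1))]² / (p0 − p1)², with p̄ the mean of p0 and p1.

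- Objective 1: p1 = 0.57 × 0.83 = 0.4731, which gives 557 at 90% power and 416 at 80%.
- Objective 2: p1 = 0.225 × 0.70 = 0.1575, which gives 532 at 80% power and 712 at 90%.

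All four agree with the protocol's tables. With continuity correction the two design figures would be 577 and 561, which do not agree.

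**Step 2: power at the planned numbers.**

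Power = Φ{[(p0 − p1)√n − 1.96·√(2p̄(1−p̄))] / √(p0(1−p0) + p1(1−p1))}

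This gives 92.0% for Objective 1 at 600 per arm and 80.0% for Objective 2 at 532 per arm.

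**Step 3: dilution.** Unmessaged intervention men are taken to have the control risk, and the same share f is applied to both objectives:

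p1* = p1(1 − f) + p0·f

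Example at f = 5%: Objective 1, 0.4731 × 0.95 + 0.57 × 0.05 = 0.4779, relative risk 0.8385. Objective 2, 0.1575 × 0.95 + 0.225 × 0.05 = 0.1609, relative risk 0.715.

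| f (assumed) | Men of 600 | Obj. 1 RR | Obj. 1 power | Obj. 2 RR | Obj. 2 power |
|---|---|---|---|---|---|
| 0 | 0 | 0.830 | 92.0% | 0.700 | 80.0% |
| 1% | 6 | 0.832 | 91.5% | 0.703 | 79.2% |
| 2% | 12 | 0.833 | 91.0% | 0.706 | 78.3% |
| 5% | 30 | 0.839 | 89.2% | 0.715 | 75.6% |
| 10% | 60 | 0.847 | 85.8% | 0.730 | 70.7% |

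Objective 1 stays at or above 90% up to f of about 3.7%, or about 22 men (0.037 × 600). Objective 2 has no reserve.

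**Step 4: unequal loss.** With the same total of 1,064 men at day 42 but 562 controls and 502 intervention men, Objective 2 power is 79.8%. If loss did differ by arm, the worry would be selection bias, not power.

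**The case against.** The case against has real weight.

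- **Failures are probably few.** The text is sent from the man's own phone, on airtime loaded by the study, before he leaves the clinic. A failed text can be noticed and repeated. The clinic file also holds his number and the database his arm, so a failed text need not mean no messages. The protocol plans a manual of operations, which could cover this. All of this stands, and it is why the lower rows of the table are the more plausible ones.
- **Keeping unreached men is right.** A reader might infer that the intent-to-treat analysis is at fault. It is not. Retention preserves the randomised comparison, the dilution is conservative, and the protocol describes the chosen design as nearer to an effectiveness study.
- **Contact quality by arm.** A reader might infer that staff secure better numbers in the intervention arm and that loss to follow-up will differ. The documents do not support this. Registration and airtime are described for all participants (6.2; Cost of Intervention). The number is abstracted from the clinic file before the envelope. An alternate number is requested (11.0), and call-backs run twice daily for seven days (9.1), both without distinction by arm. Unequal effort remains only a possibility.
- **Later loss of contact.** Lost phones and changed numbers dilute the effect in the same way, and reordering the visit does not prevent that.

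None of this gives a reason to prefer registration after allocation. That the arm is listed in the text in 5.2 but not in 6.2 suggests that the order is a software convenience.

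**Conclusion.** The point holds as a cheap improvement, not as a flaw that threatens validity. The protocol's narrative places the step on which message delivery depends after the arm is known. At 2% to 5% never messaged, the loss is about 1 to 3 percentage points of power for Objective 1 (92.0% to 91.0% or 89.2%) and about 2 to 4 for Objective 2 (80.0% to 78.3% or 75.6%). These figures rest on an assumed failure rate, on unmessaged men having the control risk, and on the planned control risks and relative risks being true. The one firm statement about size is that Objective 2 is planned at almost exactly 80%, so under these assumptions any non-delivery takes it below the stated minimum. Differential contact between arms is not established and should not be reported as a finding.

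**What to change.** 1. In Allocation concealment (5.1) and Enrollment Visit (6.2), place the registration text (number, time of day, language) before the envelope is opened, and make its success a condition for randomisation in both arms. The airtime top-up moves with it.
2. In the Study Registration Module of the schematic (5.2), remove the study arm from the text, so that its content matches 6.2.
3. Pass the arm to the messaging software after allocation, either through the research assistant's database entry, which 5.1 already requires, or through a short code sent by staff. The first route needs a link from the database to the messaging platform that the protocol does not describe; the second avoids it.

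Cost: reordered steps within one visit and a small software change. The condition acts as one more eligibility requirement, so a few men who cannot register are not randomised and must be replaced. In return, every randomised man starts with a confirmed link, and the check is done before anyone knows the arm.

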## Follow-up Visit

According to the Kenya national guidelines for comprehensive male circumcision services [26], circumcised men are required to visit the clinic at 7 days post-procedure. At this visit, the wound is examined for healing progress, signs of infection, and signs of other post-operative surgical complications. Additional examinations and/or referral are done based on the man’s symptoms. All clinic procedures are documented in the patient’s clinic records. These clinical procedures are not study procedures. Our study will only be interested in extracting data from clinic records.

After the 7th post-operative day, study staff will check participants’ clinic records to ascertain their attendance of this visit and to allow for assessment of study outcome measures. A 3-day window before and after the date of the scheduled visit is allowed. Study staff will abstract data from participants’ clinic records. The data collected will include: *date of visit, date of circumcision, type of visit (routine/client-initiated/physician-scheduled), adverse events (event, grade, treatment), resumption of sexual intercourse, days since resumption, and satisfaction with MC procedure*. HIV status and/or test results will NOT be collected as part of this study.

After the scheduled 7-day post-operative visit, participants in the intervention arm will receive one text message on each of the following days post-procedure: days 8, 14, 21, 28, 35, 41 and 42.

## Final Study Visit (Virtual Visit)

At 42 days post-procedure, a final intervention text message will be sent to participants randomized to the intervention arm. After the final SMS at day 42, participants in both arms will be interviewed via phone call to determine outcome data for our second primary objective (appendix IV). All participants will also be invited to visit the clinic should they wish to receive free condoms

At conclusion of the randomized controlled trial, a subset of participants who failed to return for the scheduled 7-day post-operative visit will be invited to take part in a phone interview to ascertain reasons for failure to return. A brief questionnaire (similar to the baseline questionnaire, appendix III) will be administered via phone interview. Items in this questionnaire will allow for assessment of secondary study outcome measures. Responding to this questionnaire will terminate study participation.

## Study Withdrawal for Participants

Participants will be free to withdraw from the study at any time by presenting to the study clinic and indicating their desire to withdraw. Reasons for study withdrawal will be ascertained. Where possible, information on study primary and secondary endpoints will be evaluated at the time of study withdrawal. No further messages will be sent, or phone calls made, to a participant who deliberately withdraws from the study.

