### Inferential analyses

The primary analysis will follow the intent-to-treat principle, that is, we will analyze the arm to which the subject was randomly assigned. All tests will be conducted at the 5% significance level (two-sided).

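### The only exit described ends both the messages and the outcome call, so a man in the SMS arm who wants the texts to stop can be lost to a primary outcome

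*Protocol*

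**What the plan says.** Section 6.5 lets men leave at any time "by presenting to the study clinic and indicating their desire to withdraw". After that, "No further messages will be sent, or phone calls made, to a participant who deliberately withdraws from the study". The same section asks for reasons for withdrawal and adds: "Where possible, information on study primary and secondary endpoints will be evaluated at the time of study withdrawal".

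Four other places give this rule its effect:

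- **Who gets messages (5.2, Text Messaging Regimen).** The software will "send out one text message daily to participants in the intervention arm for the first seven days post-procedure", and then on days 8, 14, 21, 28, 35, 41 and 42. That is 14 messages, in one arm only.
- **No reply channel (5.2, Cost of Intervention).** "Because the SMS system is only one way", so a man cannot text back to stop.
- **Source of the second primary outcome (6.4).** Both arms are interviewed by phone after day 42.
- **Handling of missing men (10.2, Sensitivity Analyses).** Men without the day-42 assessment are left out of the Objective 2 analyses. Imputation under several assumptions is a sensitivity analysis.

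On the analysis set, section 10.2 says: "The primary analysis will follow the intent-to-treat principle".

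**The concern.** Stopping an intervention and leaving follow-up are different decisions, and section 6.5 offers them only as a package. An SMS-arm man who wants the texts to end, but would take one call five weeks later, has no such choice. A control man has no texts to stop and so lacks this reason to leave.

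The protocol foresees a motive. Its sections on shared phones, risks and limitations all discuss personal information being exposed when a phone is shared.

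At stake is the comparison of early resumption of sex between arms. Analysis by assigned arm keeps the balance of randomization only if outcomes are sought for everyone who has not refused follow-up. Loss that depends on the arm, among men who may differ in their risk of resuming sex, can shift the result either way. Imputation cannot recover calls that were never made.

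**Working it through.** **Step 1. Reproduce the plan's figure.** Section 10.1 gives, for Objective 2, a control rate of 0.225, relative risk 0.70 (so 0.1575 in the SMS arm), two-sided 5% and 80% power.

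n = [1.96 × √(2 × 0.19125 × 0.80875) + 0.84 × √(0.225 × 0.775 + 0.1575 × 0.8425)]² / (0.225 − 0.1575)² = 532 per arm after rounding up, as stated. Going from 600 to 532 is a loss of 68 men, or 11.3%, planned as equal in both arms.

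**Step 2. Set the rules side by side.** The described exit ends calls (6.5). The outcome needs the call (6.4). No call means exclusion from Objective 2 (10.2). Only SMS men can want messages stopped (5.2). So stopping the intervention costs a primary outcome, in one arm only.

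**Step 3. Ask what the capture of endpoints at withdrawal recovers.** A man who has already resumed sex has a known outcome. A man who leaves on, say, day 10 without having resumed has an unknown day-42 status. The provision helps in part only.

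**Step 4. Illustrate the size with no true effect.** The protocol gives no withdrawal rate, so two inputs are assumptions: w, the share of the SMS arm that leaves, and r, the share of those leavers who would resume early. With 0.225 in both arms, the complete-case SMS rate is (0.225 − w × r)/(1 − w), and the relative risk is that rate divided by 0.225. The false-positive rate uses a normal approximation, with the planned 11.3% loss applied to the remaining men in each arm.

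| w | r | SMS rate | RR | False-positive rate |
|---|---|---|---|---|
| 1% (6 men) | 0.45 | 0.2227 | 0.99 | 5.1% |
| 2% (12 men) | 0.675 | 0.2158 | 0.96 | 6.5% |
| 5% (30 men) | 0 | 0.2368 | 1.05 | 7.4% |
| 5% | 0.45 | 0.2132 | 0.95 | 7.4% |
| 5% | 0.675 | 0.2013 | 0.90 | 15.0% |

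For example, with w = 5% and r = 0.675: (0.225 − 0.03375)/0.95 = 0.2013, and 0.2013/0.225 = 0.895. The values 0.45 and 0.675 are twice and three times the control rate.

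**Step 5. Power.** The lost numbers matter little. Power at relative risk 0.70 goes from 80.0% to 78.9% with 5% leaving and 77.7% with 10%. The issue is possible bias, not sample size.

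**The case against.** Much can be said for the plan. Messages need no reply, so a man can ignore them and still be called. Having to come in person probably keeps formal withdrawals few. Men are shown example messages and enrolled only if they accept them. Section 10.2 compares lost with retained men, adjusts for imbalance among the retained, and imputes, including a version that counts missing as failure. Not calling a man who has withdrawn respects his decision. The consent form, which is not in the public text, may name another route. All of this stands, and it limits the likely size. It does not create the missing option, and the analyses listed work only with whatever data were collected.

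Three stronger readings are tempting, and the protocol supports none of them.

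- *Withdrawal visits inflate 7-day attendance.* If 12 SMS men (2%) who would otherwise not attend were all counted as attending, the Objective 1 comparison would be 0.57 against 0.55, and the false-positive rate about 11%. That requires visits inside the window of day 7 plus or minus 3, an entry in the routine clinic record, and no separation by the visit type that section 6.3 abstracts. Nothing says a withdrawal contact enters that record. A man examined while there did attend.
- *Men who leave early are counted as abstinent.* No section codes an early report of no sex as not resumed. The trial profile and the sensitivity analyses treat men without the outcome as lost.
- *The rule favours the SMS arm.* The direction depends on who leaves. With low-risk leavers the relative risk moves above 1, as the r = 0 row shows.

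**Conclusion.** The defect holds as a possibility built into a stated rule. The one exit described ties stopping messages to giving up the day-42 outcome, and only the SMS arm has messages to stop. A reader might infer that the trial will lose outcomes selectively. The protocol does not show that, since it gives no withdrawal rate or reasons by arm.

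Under the assumed rates the effect is minor at 1-2% withdrawal. It could matter at 5% with strongly selected leavers, where a false-positive rate of 15% replaces the nominal 5%. That 5% is 30 men, nearly half of the 68 lost per arm in the plan, so it is towards the high end for in-person withdrawals alone. Even then, a relative risk of 0.90 is far from the 0.70 the trial is sized to detect.

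The change is still worth making. The loss is avoidable, it falls on a primary outcome, and it arises in data collection, where no later analysis can restore it.

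**What to change.** In section 6.5 and the consent form:

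1. Accept requests by telephone as well as in person.
2. Record a request to stop messages separately from withdrawal from follow-up, and report both by arm.
3. For a man who only stops messages, keep the day-7 record abstraction and the day-42 call, with his agreement. Bar calls only for men who withdraw from follow-up.

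As a precaution, add two sentences: a contact made only to withdraw is not 7-day attendance; and a report of no sex made before day 42 leaves day-42 status missing, censored at the date of the report.

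The cost is small changes to protocol and consent wording and one form field. The calls kept are ones the plan already includes.
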